### Implementation {16c}

Randomisation of clusters was performed at the Institute of Medical Biometry and Statistics, Faculty of Medicine and Medical Center – University of Freiburg, Germany. Participants are enrolled by study nurses. Allocation to the intervention or control group is determined by the stepped-wedge design: At the beginning of the study, all sites recruited into the control group. After the first period, one site switched to intervention conditions. At intervals of 50 days, clusters 2 to 8 also switch to the intervention phase.

## Assignment of interventions: blinding

### Who will be blinded {17a}

Due to the study design and the type of intervention, no blinding is possible.

### Procedure for unblinding if needed {17b}

Not applicable, since no blinding is used.

## Data collection and management

### Plans for assessment and collection of outcomes {18a}

#### Baseline

Data on laboratory measurements (serum creatinine and HbA1c), blood pressure, pre-existing illnesses and medication are taken from the patient’s medical record in the hospital information system (HIS). Additional data on demography, height and weight, smoking status and housing as well as self-assessed health status and health literacy is collected by questionnaire during the hospital stay. Only blood analysis values from the respective laboratory at each site are used. Serum creatinine is measured according to Jaffé.

#### Follow-up at 3 months

Patients in the intervention group receive a mailed questionnaire and are asked to state whether they attended the appointment by the nephrologist and how they rate its benefit. Additionally, the standard questionnaires SF12, PIKS and B-IPQ are used for the patient-reported outcomes (PRO).

#### Follow-up at 12 months

All study patients are asked about their perceived quality of care, their perception of the disease (B-IPQ), their level of information about the disease (PIKS) and their quality of life (SF12).

Follow-up data on laboratory measurements, incident diabetes and medication is collected from the GPs and/or nephrologists by post/fax/email. Physicians receive financial compensation for their efforts.

#### Acceptance and feasibility

Interviews with 8 GPs and 4 nephrologists with their assessments of the risk-based appointment system for hospital patients are recorded and analysed.

### Plans to promote participant retention and complete follow-up {18b}

The recruited patients in the intervention group are reminded of their appointment with the nephrologist and are offered to get a second appointment if they have not been able to attend the initially organised visit. About 11 months after hospital discharge, all patients are asked by postal mail to make an appointment with their GPs or nephrologists if possible. This shall ensure that primary and secondary endpoint information will be available. The GPs and nephrologists consulted are initially and repeatedly informed about the course of the study. These medical colleagues will receive an expense allowance for participating in the study according to the current fee schedule for physicians, e.g. for providing data. If the follow-up questionnaire is not returned by a physician within a month, they will be contacted by telephone and the documents may be sent again by post or fax. Participants are equally contacted by phone if they do not return the follow-up questionnaire in time. The questionnaire then can be administered by telephone.

### Data management {19}

The study-related data from the HIS, the baseline patient questionnaire, the follow-up questionnaires and the information from the GP and specialist at the 12-month follow-up are recorded in the eCRF (Clincase). The data is entered by trained study nurses. Access to the data entry screens is password-protected. The eCRF includes an audit trail to document any data changes.

Data plausibility is checked on data entry into the eCRF with automatically generated queries. Additionally, more advanced data checks are programmed in SAS 9.4 (SAS Inc. Cary, NC, USA) and are run on a weekly basis. Resulting queries are returned to the study nurses for completion.

### Confidentiality {27}

The data is stored in the eCRF software Clincase. Study documents (questionnaires, information sheets, data collection sheets in exchange with the physicians in the follow-up) are scanned and stored in the HIS. The original sheets are stored in locked cabinets. Only the study nurses and the study doctors have access to patient data in the HIS and to the cabinets.

### Plans for collection, laboratory evaluation and storage of biological specimens for genetic or molecular analysis in this trial/future use {33}

Not applicable; no biological specimens are collected for genetic or molecular analysis.

## Statistical methods

### Statistical methods for primary and secondary outcomes {20a}

In the confirmatory primary analysis, the effect of the intervention on the primary endpoint (decrease in eGFR at 12 months) is tested in a linear mixed model, estimated and reported with a one-sided 95% confidence interval ([23]). The model includes the intervention (with versus without modified discharge management), the categorical periods as fixed effects, the baseline measure of eGFR, age at study inclusion and gender as covariates. Intra-cluster variation, i.e. membership of a cluster, is modelled via random intercept. The one-sided test to prove the benefit of the intervention is performed based on the respective one-sided 95% confidence interval from the linear mixed model. Since the follow-up examination will not always take place exactly 12 months after discharge, the decrease in eGFR from the baseline to the follow-up measurement (i.e. the dependent variable in the regression model) is proportionally converted to a 12-month difference.

Intervention effects for binary secondary outcomes will be estimated and tested similarly, using appropriate generalised linear mixed models.

#### Health economic evaluation

The health economic evaluation examines the relationship between the additional costs and the additional benefits of the intervention using classic cost-effectiveness analyses. The short-run costs of the intervention (calculation of the 5-year risk of kidney failure and making an appointment with a specialist) are derived from the documented workload of the nursing staff involved. The costs of the medication during the 12-month follow-up are approximated from the medication plan at 12 months after discharge. Lastly, the costs of GP and specialist visits during the 12-month follow-up are calculated based on standardised unit costs [24].

After summarizing these costs on the patient level, a cost-cost comparison between the intervention and control group is carried out using linear mixed models, analogously to the analysis scheme described above. Finally, the additional costs of the intervention derived from this are compared with the results of the analyses regarding the primary and secondary endpoints. For inference, a 95% confidence interval is calculated for the individual cost-effectiveness ratios, e.g. for the additional costs per eGFR improvement, using Fieller's theorem ([25, 26]).

#### Process quality

The percentage of patients with a nephrology specialist consultation within 3 months of discharge in both groups is compared descriptively. The perceived quality of care, reasons for not consulting a nephrologist, subjective concept of illness, knowledge of kidney disease and health-related quality of life in the intervention patients group are also presented descriptively. Subjective disease concept, knowledge about kidney disease and health-related quality of life 12 months after discharge are compared between the intervention and control groups.

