### Eligibility criteria {10}

#### Inclusion criteria

Age ≥ 18 yearsAdmitted to one of the participating hospitalsHealth insured with ‘Knappschaft-Bahn-See’Existing chronic renal disease (either already known and documented in the hospital information system as diagnoses ICD-10 N04.9, N17.99, N18.1–9, N19, R31, R80, or identified during hospitalisation (as distinct from acute renal failure))Risk of end-stage renal disease within 5 years according to KFRE score of at least 15% (date of laboratory determination before 20 June 2023) or at least 9% (since 20 June 2023), respectively; see the section ‘Participant timeline {13}’ for details on this change.Consent to contacting the general practitioner (GP) and specialists after dischargeGeneral state of health sufficient for study participation

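### The 3-month nephrology consultation proportion is set down for a descriptive comparison of arms that differ in calendar time and entry cut-off; it should use the period-adjusted model already planned for binary secondary outcomes

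*Protocol article*

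**What the plan says.** The article ties three groups of outcomes to a model suited to the design. In Statistical methods for primary and secondary outcomes {20a}, the primary model includes "the categorical periods as fixed effects, the baseline measure of eGFR, age at study inclusion and gender as covariates", with a random intercept for centre. Binary secondary outcomes follow: "Intervention effects for binary secondary outcomes will be estimated and tested similarly, using appropriate generalised linear mixed models". In Health economic evaluation, costs are compared "using linear mixed models, analogously to the analysis scheme described above".

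The Process quality section has no such link. For specialist consultation it fixes the method: "The percentage of patients with a nephrology specialist consultation within 3 months of discharge in both groups is compared descriptively". For illness perception (BIPQ), kidney knowledge (PIKS) and quality of life (SF12) it says: "Subjective disease concept, knowledge about kidney disease and health-related quality of life 12 months after discharge are compared between the intervention and control groups". That sentence names no method.

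Two features of the design bear on this. Implementation {16c} says: "At the beginning of the study, all sites recruited into the control group"; one centre switches after the first period and the others follow at 50-day intervals. The inclusion criteria require a KFRE risk of "at least 15% (date of laboratory determination before 20 June 2023) or at least 9% (since 20 June 2023), respectively".

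**The concern.** In a stepped-wedge trial, control patients are mostly early and intervention patients mostly late. A comparison without period terms therefore carries any change over time in referral practice or in the patients enrolled. Here there is a known change in who could enter, and the article's Discussion says the cut-off was lowered because participants differed from the intended population, notably in age. Age and renal risk could plausibly affect whether a patient sees a nephrologist under usual care.

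The outcome matters. Objectives {7} has two parts: that the scheme brings patients to specialist care according to need, and that it slows eGFR decline. Of the listed endpoints, the 3-month consultation difference measures the first part most directly. A raw difference could overstate or hide the effect, and the documents do not allow the direction to be predicted.

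**Working it through.** **Inputs (all from the protocol article).** Recruitment runs from 1 October 2022 to 15 August 2024 (Trial status). Nine phases of 50 days were planned, and the first was extended by 5 weeks to 85 days (Trial design {8}). Four phases of 50 days were added (Recruitment {15}). One centre switches after phase 1 and one more every 50 days (Implementation {16c}). The cut-off changed on 20 June 2023 (Inclusion criteria).

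**Reproducing the plan's calendar.** 85 + 12 × 50 = 685 days. Counted from 1 October 2022, day 685 is 15 August 2024, as stated. Phase 5 then runs from 24 May to 12 July 2023, so 20 June is its day 28: 27 days fall before the change and 23 from it onwards.

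**Centre-days = days in phase × centres in that condition.** The cut-off applies by date of laboratory determination, taken here as the calendar day.

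| Phase | Days | Control / intervention centres | Control centre-days | Intervention centre-days |
|---|---|---|---|---|
| 1 | 85 | 8 / 0 | 680 | 0 |
| 2 | 50 | 7 / 1 | 350 | 50 |
| 3 | 50 | 6 / 2 | 300 | 100 |
| 4 | 50 | 5 / 3 | 250 | 150 |
| 5, to 19 June | 27 | 4 / 4 | 108 | 108 |
| **15% rule** | | | **1,688** | **408** |
| 5, from 20 June | 23 | 4 / 4 | 92 | 92 |
| 6 | 50 | 3 / 5 | 150 | 250 |
| 7 | 50 | 2 / 6 | 100 | 300 |
| 8 | 50 | 1 / 7 | 50 | 350 |
| 9 to 13 | 250 | 0 / 8 | 0 | 2,000 |
| **9% rule** | | | **392** | **2,992** |
| **Total** | | | **2,080** | **3,400** |

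**Shares.**
- Control under the 15% rule: 1,688 / 2,080 = 81%.
- Intervention under the 15% rule: 408 / 3,400 = 12%.
- Intervention with no concurrent control: 2,000 / 3,400 = 59%.

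**What a raw contrast carries.** The share under the 9% rule is 88% in intervention and 19% in control. If the usual-care consultation proportion differs by a step S between the two eras, the raw difference contains (0.88 − 0.19) × S ≈ 0.69 × S. The documents give no value for S. If it were 10 percentage points (an assumption for scale only), the distortion would be about 6.9 points.

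**Sensitivity.** Let recruitment per centre-day rise by a factor r after the change (assumed). The early control share is 1,688 / (1,688 + 392r), and the late intervention share is 2,992r / (408 + 2,992r).
- r = 2: 68% and 94%.
- r = 3: 59% and 96%.
- The control majority under the 15% rule is lost only when r exceeds 1,688 / 392 ≈ 4.3.

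The unequal site sizes expected in Sample size {14} (77, 63, 50, 37, 37, 34, 25, 17) were applied to 3,000 random switching orders, keeping those within the stated 20-subject balance limit. With r = 1, the early control share lies between 76% and 87% and the late intervention share between 85% and 92%.

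**The case against.** The strongest reply is that this is ordinary process reporting. Consultation is listed under process quality, not among the secondary endpoints. No test is attached to it, and a raw percentage by arm is a normal way to show uptake. Table 1 also collects dated specialist visits, and their costs enter an adjusted mixed-model comparison, so specialist use is not left wholly unadjusted. This stands as a limit on severity. It does not remove the point: the article lists a between-arm difference in this proportion and fixes a method that cannot separate the scheme from time.

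Four further objections are correct and bound the finding.

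- **Patient-reported outcomes.** A reader might infer that these are also fixed as crude comparisons. The documents do not support that. The sentence names no method, omits the word used for consultation, and does not exclude the mixed model; a condensed article may leave this to an analysis plan that is not shown.
- **Subgroup analysis.** A reader might infer that the planned analysis of patients at 15% risk or above leaves these outcomes out. Methods for additional analyses {20b} restricts it to no outcome, so silence is not exclusion. That subgroup would not remove calendar confounding in any case.
- **Case mix.** Patients enrolled under the 9% rule are not all below 15%. No risk distribution is given, and nothing shows in which direction the later patients would differ in health, knowledge or referral.
- **Centre-days.** The 81% and 12% are not patient proportions. Site sizes and recruitment rates vary, though the imbalance keeps its direction under the variations tried.

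**Conclusion.** The point holds for the 3-month consultation proportion. Carried out as written, the comparison sets mostly early controls, recruited largely under the 15% rule, against mostly late intervention patients, recruited largely under the 9% rule. At equal recruitment per centre-day the imbalance is 81% against 12% under the 15% rule, with 59% of intervention centre-days lacking concurrent control. The resulting bias in the consultation difference cannot be computed, because neither the secular trend nor the case-mix shift is given.

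For the 12-month BIPQ, PIKS and SF12 comparisons the finding is weaker. No adjustment is stated, and Table 1 shows no baseline measurement, so change from baseline is not available as a safeguard.

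A reader might take this as a threat to the trial's main result. It is not: the primary endpoint, the binary secondary outcomes and the costs are all assigned mixed-model analyses. This is an inexpensive improvement to a non-confirmatory outcome.

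**What to change.** In the Process quality section:

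1. Estimate the between-arm difference in 3-month consultation with the generalised linear mixed model already planned for binary secondary outcomes: period as fixed effect, random centre intercept, baseline eGFR, age and gender.
2. Add an indicator for the cut-off era or the KFRE score. Period effects absorb the cut-off change in every phase except phase 5, where it falls mid-phase. The KFRE score overlaps with eGFR, age and sex, from which it is partly built, so the era indicator is the simpler choice.
3. Show raw percentages by arm only as description, labelled as confounded with calendar time and the entry rule.
4. State that the 12-month BIPQ, PIKS and SF12 comparisons use the same period and centre adjustment, in linear form.

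Restricting a raw comparison to phases 2 to 8 is not a substitute. Across those phases control centres fall from seven to one while intervention centres rise from one to seven, so time confounding remains, and 59% of intervention centre-days are lost.

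The cost is a sentence or two of analysis wording and reuse of planned model code, with wider intervals than the raw comparison would give. Phases 9 to 13 contribute no within-period contrast to the adjusted estimate, so the later intervention patients add less precision than their number suggests.

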#### Acceptance and feasibility

To evaluate the acceptance and feasibility of the new intervention, the risk-based appointment scheduling, semi-structured interviews with the participating nephrologists and GPs will be conducted. With individual interviews, we aim to explore the nephrologists and GPs appraisal of the intervention. Therefore, interview guidelines will be developed for each of the two groups, starting with an open narrative question followed by questions concerning the themes of interest. These include the doctors’ experiences with the new intervention, the appraisal of individually perceived benefits and costs of the intervention, the cost–benefit ratio, possible improvements in the collaboration between the different care sectors (hospital, nephrology specialists, GPs) through the intervention, perceived feasibility in routine care and ideas for optimizing the intervention. Parts of the interview guidelines for the nephrologists and GPs will be the same to obtain the different perspectives on the risk-based appointment scheduling. In addition, the interview guidelines will consist of specific questions for the two groups. We aim to interview *N* = 4 nephrologists and *N* = 8 GPs. A purposeful sampling method will be used to achieve maximum variation within the sample, as intended in qualitative research. Pre-defined selection criteria such as age, gender, work experience, or urban vs. rural region of the location of the practice will be considered. The doctors should take care of at least one study patient. A trained project research associate who is not involved in the intervention provision will conduct the interviews. The interviews will take place in parallel with the intervention phase. It is estimated that the interviews with the nephrologists will last about 30 min and the interviews with the GPs 20 min. The interviews will be audio-recorded and transcribed verbatim. The transcribed interviews will be analysed following qualitative content analysis (cf. [27]). In this method of content structuring, the data material is categorised and coded in an iterative process using an inductive and deductive approach. To ensure a transparent, replicable analysis procedure, coding rules with anchor examples will be documented. The Theoretical Framework of Acceptability (TFA; [28]) will guide the development of the interview guidelines and the analysis.

### Interim analyses {21b}

Since the intervention consists of providing an appointment with a nephrology specialist as part of hospital discharge management and the control patients receive no study-related intervention, there is no need for interim analyses concerning a possible early termination of the trial. However, during recruitment and follow-up, analyses are performed concerning the data quality.

### Methods for additional analyses (e.g. subgroup analyses) {20b}

Since the cut-off value to identify patients with an increased risk of end-stage renal disease within 5 years was changed from 15 to 9% during the recruitment period (see the section ‘Participant timeline {13}’ for details), an additional subgroup analysis will be performed, focusing on the originally planned collective of patients with risk score ≥ 15%.

### Methods in analysis to handle protocol non-adherence and any statistical methods to handle missing data {20c}

Participants are analysed ‘as randomised’ (being cluster-randomised instead of randomised individually), independent of their medical treatment after hospital discharge. Participants without 12-month follow-up are reported in a CONSORT flowchart. Missing data of these participants are accounted for in the evaluation under the missing at random assumption.

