### Outcomes {12}

#### Primary endpoint

Difference in mean change in eGFR in ml/min/1.73 m^2^ (after chronic kidney disease epidemiology collaboration [CKD-EPI]) between the intervention and control group from baseline to 12 months after hospital discharge

The eGFR was chosen as the primary parameter because it is considered a good indicator for the assessment of kidney patients and has also been used in numerous nephrology studies over time [18].

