#### Secondary endpoints

Differences between intervention and control group, 12 months after hospital discharge:Difference in proportion (%) of patients with controlled blood pressure (≤ 140/90 mmHG)For diabetics: difference in proportion (%) with guideline-compliant HbA1c (6.5 to ≤ 7.5%)Difference in proportion (%) of patients with non-guideline-compliant care about the prescription of selected medication groups (including statins, RAS blockers, ARBs and ACEIs; based on pre-specified ATC codes classified as non-guideline-compliant) according to the assessment of medication plans by consultant nephrologistsDifference in the proportion (%) of patients with non-guideline-compliant medication (resulting from the aforementioned assessment of medication plans by several consultant nephrologists)Difference in the mortality rate (%)

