##### Twelve-month follow-up (all patients)

One year after discharge from the hospital, a follow-up is performed for each patient regarding renal function, HbA1c, blood pressure, medication, frequency of physician visits, quality of life, knowledge about the disease and illness perception. For this purpose, the GP and/or nephrologist are contacted by the study nurse by mail and/or phone to check the vital status of the patient and to request laboratory data concerning serum creatinine and Hba1c in diabetic patients, as well as the latest three blood pressure measurements, the number of patients visits during the last year, incident diabetes and the actual medication (via the standardised medication plan). The medication is assessed whether relevant medication classes are included (antihypertensives, statins, ACE inhibitors or RAAS blockers, and SGLT2).

The data collected at the 3-month and 12-month follow-ups are detailed in Table 1, together with the baseline data.

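### The primary analysis treats participants who died like any other missing follow-up, and dialysis or transplant is not among the listed 12-month data, so creatinine taken on dialysis could count as valid eGFR

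*Protocol article*

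**What the plan says.** The primary endpoint (Outcomes {12}) is the difference in mean change of CKD-EPI eGFR "between the intervention and control group from baseline to 12 months after hospital discharge". Under Statistical methods {20a}, the effect "is tested in a linear mixed model, estimated and reported with a one-sided 95% confidence interval". The model has fixed effects for intervention and period, covariates for baseline eGFR, age and gender, and a random intercept for cluster. Because follow-up will not fall exactly at 12 months, the decrease "is proportionally converted to a 12-month difference".

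On incomplete follow-up, section {20c} has two sentences: "Participants without 12-month follow-up are reported in a CONSORT flowchart", and then "Missing data of these participants are accounted for in the evaluation under the missing at random assumption". No reason for the missing value is distinguished.

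At 12 months the study nurse contacts the GP and/or nephrologist "to check the vital status of the patient and to request laboratory data concerning serum creatinine", together with HbA1c in diabetics, blood pressure, number of visits, incident diabetes and medication (Twelve-month follow-up). Table 1 lists vital status at this time point. Neither place lists dialysis, transplant or end-stage renal disease. Death appears among the secondary endpoints as "Difference in the mortality rate", with no link to the primary analysis.

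**The concern.** Two different problems meet in one outcome variable.

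First, after death there is no eGFR that could have been observed. Missing at random lets participants with values stand in for similar participants without them. Applied to deaths, it assigns a renal course to people who no longer have one. Each patient has a single post-baseline value. A likelihood-based mixed model would therefore leave those without a value out, while imputation would give them the course of comparable survivors. The article does not say which is meant, but neither separates a death from a lost form.

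Second, a patient who starts dialysis may still return a creatinine. Dialysis lowers creatinine, so CKD-EPI then no longer measures the patient's own kidney function and can make kidney failure look like preserved function. If the dialysed patient has no value, the value is missing because of the outcome itself. Without a dialysis field the analyst cannot tell these cases from any other, and no later analysis plan can recover a variable that was not collected.

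At stake is the meaning of the primary estimate in a trial whose entry criterion is the risk of kidney failure.

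**Working it through.** **Inputs from the article.** Target difference 2 and SD 4 ml/min/1.73 m², 340 complete observations, 20% drop-out, later 286 complete observations with 72.1% power at one-sided 5% (Sample size {14}). Entry threshold: five-year KFRE risk of at least 15%, later at least 9% (Eligibility criteria {10}).

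**The plan's own figures.**
- Enrolment: 340 / 0.8 = 425, as stated.
- Second power update: 72.1% power implies SE = 2 / (1.645 + 0.586) = 0.897. The effect detectable at 80% power is then 0.897 × (1.645 + 0.842) = 2.23, as stated.

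The concern does not touch these figures.

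**How many participants fall under the rule.** 286 / 0.8 = 357.5, so about 358 enrolled and about 72 without 12-month follow-up. The article does not say how many of these would be deaths.

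**Kidney failures in year 1.** No rate is given. Assuming a constant hazard, one-year risk = 1 − (1 − five-year risk)^(1/5):

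| Five-year risk | One-year risk | Expected among 357.5 |
|---|---|---|
| 9% (current threshold) | 1.9% | 6.7 |
| 15% (earlier threshold) | 3.2% | 11.4 |
| 25% (assumed mean) | 5.6% | 20.0 |

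The first two rows are near a minimum, because the thresholds are floors for entry. Deaths come on top. How the kidney failures divide between participants with a returned creatinine and participants without one is unknown.

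**Size of the distortion.** If patients with the event would have declined by D more than the others, and their share differs between the arms by Δq, the contribution left out of the treatment contrast is Δq × D. Both are assumptions:
- low corner: 0.01 × 5 = 0.05
- 0.01 × 8 = 0.08
- 0.02 × 10 = 0.20
- 0.05 × 10 = 0.50
- high corner: 0.05 × 12 = 0.60

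That is roughly 0.1 to 0.6 ml/min/1.73 m². Against the target of 2, the high corner is 30% and the low corner 2.5%. Where a creatinine taken on dialysis is kept as valid, the same product applies, with D read as the gap between the recorded value and one that reflects kidney failure.

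**Direction.** If the intervention prevents death or dialysis, more poor courses leave the control arm and benefit is hidden. If nephrology contact brings dialysis forward, poor courses leave the intervention arm, or are masked there, and the one-sided test is favoured. The documents do not settle which applies.

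**Cost of putting an assigned low value into the primary analysis.** Take 4% of patients placed 10 ml/min/1.73 m² lower. The variance is 16 + 0.04 × 0.96 × 100 = 19.84, so the SD is 4.45. Scaling the SE in proportion gives 0.897 × 4.45 / 4 = 0.998. Power at an unchanged effect of 2 is Φ(2 / 0.998 − 1.645) = Φ(0.36), about 64% instead of 72.1%. A larger composite effect could offset this.

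**The case against.** Several stronger readings are tempting, and the documents do not carry them.

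- A reader might infer that the plan declares dialysis to be missing at random. Section {20c} names neither death nor dialysis. It covers participants without 12-month follow-up, and a dialysed patient with a creatinine is not among them.
- A reader might infer that deaths are simply dropped. The section says missing data are accounted for and names no method. Imputation, its auxiliary variables and departures from missing at random commonly belong in the analysis plan, which the Discussion mentions but which is not at hand. Their absence here is no finding.
- A reader might take the remark on patients who may not survive as a forecast of deaths. It stands under Consultation (study physicians) and is an eligibility screen. The inclusion criteria also require a sufficient general state of health.
- A reader might say that the trial cannot see dialysis at all. Nephrologists are contacted, specialist visits are recorded with dates, and patients may consent to use of insurance data {26b}. The article also gives only most of the internal protocol {31c}, so an unlisted form item is possible.
- Death is not ignored: vital status is collected and mortality is a secondary endpoint, so a survival difference would be visible beside the primary result.

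All of this limits the point. It does not remove it. The missing-at-random rule is stated without exception. Visit counts do not identify dialysis. The insurance data are optional, meant for assessment after the study, and not tied to the primary analysis. Table 1 is presented as the detail of the data collected.

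**Conclusion.** The point holds in a limited form and should be fixed. As written, deaths are handled in the primary analysis like any other missing follow-up, and the listed data do not allow a creatinine taken on dialysis to be recognised.

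The size is moderate and rests wholly on assumptions: a constant hazard for the 7 to 11 kidney failures, and assumed arm differences and excess declines for the distortion of about 0.1 to 0.6 ml/min/1.73 m². A reader might infer that a true benefit is being concealed, but the documents fix no direction of bias. For deaths, the excess decline only illustrates how far a composite could differ from the survivor estimate, since no eGFR exists after death.

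**What to change.** 1. Add to the 12-month physician form one item on kidney replacement therapy (yes/no, with date) and the date of death. Ask retrospectively for patients already followed up. Recruitment was planned to run to 15 August 2024, so at publication in June 2024 many 12-month contacts still lay ahead.
2. Do not compute eGFR from a creatinine taken on dialysis.
3. State in section {20c} that death and kidney replacement therapy are handled separately from ordinary missing data, and how each enters the primary analysis.
4. Pre-specify a sensitivity analysis beside the primary estimate. One option is a rank-based composite with death worst, then kidney replacement therapy, then eGFR change. Another is a value for dialysis patients that is fixed in advance, not taken from the observed data, and exempt from the proportional conversion to 12 months.

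The cost is a short addition to an existing form, one or two further analyses, and a convention for the ranking or the assigned value. An assigned low value in the primary analysis would change what is estimated and could lower power as shown above, so it belongs in the sensitivity analysis unless the sponsor chooses otherwise.
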